### Statistical analysis

Statistical analysis will be performed on an intention-to-treat basis using Stata software (version 13; StataCorp, College Station, TX, USA) for a two-sided type I error at α = 5%. Continuous data will be described as mean ± SD or median (IQR) according to the statistical distribution (assumption of normality studied by Shapiro-Wilk test). Categorical parameters will be described as number and percent. The primary endpoint (AUC of pain intensity based on NPRS) will be compared between groups by repeated measures analysis of variance (ANOVA) for crossover designs, taking account of the following effects: treatment group (ketamine versus placebo), sequence, subject (as random effect), and carryover. Then, the “sequence × treatment” interaction will be tested; if it is significant, statistical analysis will cover only the first period of the crossover study. The normality of residuals will be studied. When quantitative endpoints do not meet the normality assumption, a nonparametric paired Wilcoxon test will be used. Sensitivity analysis will determine the statistical nature of missing data to apply the most appropriate imputation approach.

Statistical analyses of secondary outcomes (NPSI, BPI, HAD, SF-36, PSQI and McGill Pain Questionnaire scores) will be performed similarly to those for the primary endpoint. For categorical parameters (PGIC, analgesic response), the Stuart-Maxwell test for proportion paired data or a generalized linear mixed model will be used, taking the above effects into account. Random-effects models, useful to model between- and within-subject variability, will be performed for the effects described for the crossover ANOVA, to compare the additive analgesic efficacy of associating magnesium sulfate versus placebo to ketamine, and to study the evolution of pain and analgesia with the waning of the intravenous administration. In case of omnibus *p* value < 0.05, a post hoc analysis for multiple comparisons (inflation of type I error) will be applied using the Tukey-Kramer test. For non-crossover comparisons, the usual statistical tests will be performed: (1) for quantitative parameters, ANOVA or Kruskal-Wallis test if the conditions for parametric tests are not met (normality and homoscedasticity on Fisher-Snedecor test); and (2) for categorical variables, the chi-square test or Fisher’s exact test. When appropriate (*p* < 0.05), an appropriate post hoc test will be applied: Tukey-Kramer post hoc ANOVA or Dunn post hoc Kruskal-Wallis. As discussed by Feise [47], type I error (α) will not be adjusted systematically, but rather on a case-by-case basis, in the light of clinical rather than exclusively statistical considerations.

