#### Regimen

Each patient will receive successively in random order each of the three products with a period of washout between every administration. The duration of the washout will be 5 weeks (35 days). The duration of each infusion is 2½ h per patient as follows:
*Ketamine-placebo group:* Ketamine will be administered for 2 h and placebo for 30 minutes.
*Ketamine-magnesium sulfate group:* Ketamine will be administered for 2 h and magnesium sulfate for 30 minutes.
*Placebo-placebo group:* Placebo will be administered for 2 h and placebo for 30 minutes.

The drugs used in the study (ketamine, ketamine-magnesium, and placebo) are prepared, conditioned, and released in the hospital pharmacy by one qualified person according to good manufacturing principles. Once the treatment is completed, the empty infusion bags are then returned to the packaging box, and the number of infusion bags in each dispensed container is verified and recounted at the end of the treatment by two persons totally independent of the protocol.

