### Objective

The primary objective of this study is to compare, using a crossover design, the analgesic efficacy of intravenous ketamine with that of placebo in patients with intractable NP. Secondary objectives are as follows:To compare the additive analgesic efficacy of magnesium and ketamineTo study the time course of pain and analgesia after intravenous administration of ketamine, ketamine-magnesium, and placebo

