### Allocation concealment

On the day of the first visit, inclusion and exclusion criteria are verified, and written informed consent is obtained by the physician. A clinical nurse independent from the protocol obtains the randomization number from the hospital pharmacy, and the patient is then randomized into one of the three groups. The assignment to the treatments will follow a predetermined randomization list and is generated using random blocks by a clinical research associate totally independent from the protocol. The randomization list and a copy will be edited, placed in a sealed envelope, and handed over to the Clermont-Ferrand University Hospital Pharmacy and to the coordinating center, the Clinical Research Center of Clermont-Ferrand University Hospital.

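### The primary crossover model has no period effect, so a time trend in pain inflates the error term and can trigger the switch to a period-1-only analysis

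*Protocol article*

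**What the plan says.** The Statistical analysis section specifies a repeated-measures ANOVA for crossover designs on the pain AUC and names its effects: "treatment group (ketamine versus placebo), sequence, subject (as random effect), and carryover". It then tests the sequence-by-treatment interaction and adds that "if it is significant, statistical analysis will cover only the first period of the crossover study". If normality fails, "a nonparametric paired Wilcoxon test will be used". The next paragraph analyses the secondary scores in the same way and carries the same effects into random-effects models, used among other things "to compare the additive analgesic efficacy of associating magnesium sulfate versus placebo to ketamine". Period appears as a model effect nowhere in the article.

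Under Regimen, "Each patient will receive successively in random order each of the three products", with 35 days between administrations. The set of treatment orders is not given; Allocation concealment says only that "the patient is then randomized into one of the three groups". The primary objective is to compare "the analgesic efficacy of intravenous ketamine with that of placebo in patients with intractable NP".

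**The concern.** In a crossover every patient is measured at successive times, so anything that moves pain over time moves all treatments together. A period term removes that movement from the comparison. Here the model terms are written out and period is left out, so this is a stated specification and not a detail deferred to an analysis plan.

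Three things could follow if pain drifts:

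- The drift enters the residual and enlarges the standard error.
- If the carryover term can partly stand in for time, it can shift the treatment contrast.
- The sequence-by-treatment test sees the drift as an interaction, because a given treatment falls in different periods in different orders. That would discard two thirds of the data for a reason unrelated to treatment.

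A separate gap is that the section does not say how the ketamine-magnesium periods enter the primary model.

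**Working it through.** **The plan's own figure.** The plan gives no figure for this point. Its nearest is 18 patients. The stated inputs do not reproduce that: the paired normal formula gives (38 × (2.393 + 1.282) / 57)² = 6.0, and a paired t gives 10. That is a separate matter. I use 18 (needed) and 22 (recruited) only as the planned numbers.

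**Inputs from the Sample size section.** SD 38, within-patient correlation 0.5, target difference 57, two-sided alpha 1.67%. Within-patient variance = 38² × (1 − 0.5) = 722, so within-patient SD = 26.9.

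**Assumptions, not in the documents.**
- A linear fall of d AUC units per period. The main case is d = 19, which is 19/35 = 0.54 NPRS points; the range is 5 to 35.
- Six balanced orders, or three cyclic ones.
- Interaction test at 5%.
- SD 38 (a 28-day figure) unchanged at 35 days. If it scales to 38 × 35/28 = 47.5, the same results arise at d = 23.75.

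**Step 1: standard error, no carryover term.** Period deviations from each patient's mean are d, 0, −d, a sum of squares of 2d² per patient. With balanced orders this is orthogonal to treatment, so the bias is 0 and all of it goes into the residual, which has 2n − 2 degrees of freedom. With λ = n × 2d²/722, the SE ratio is √(1 + λ/(2n − 2)). For d = 19 and n = 18: λ = 18 × 722/722 = 18, and √(1 + 18/34) = 1.24. The true SD of the contrast is 26.9 × √(2/18) = 9.0, so the reported SE is about 11.1. Rejection under no effect is about 0.4% at nominal 1.67%.

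**Step 2: how often the fallback rule fires.** In a model without period, the same λ is the noncentrality of the sequence-by-treatment F test: 10 numerator degrees of freedom with six orders, and 24 (n = 18) or 32 (n = 22) for error.

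| Drift d | SE ratio (n = 18) | Rule fires, n = 18 | Rule fires, n = 22 |
|---|---|---|---|
| 5 | 1.02 | 8% | 9% |
| 10 | 1.07 | 19% | 25% |
| 19 | 1.24 | 67% | 82% |
| 35 | 1.67 | over 99% | over 99% |

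Simulation at d = 19 gave 68% and 82%. With period in the model the rate is about 5% throughout.

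**Step 3: dependence on the carryover coding** (d = 19, n = 18; λ is the part of the drift that the model leaves unexplained). The article lists carryover but fixes no coding.

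| Carryover coding | Orders | Bias | λ | SE ratio | F df | Rule fires |
|---|---|---|---|---|---|---|
| None | six | 0 | 18 | 1.24 | 10, 24 | 67% |
| None | three | 0 | 18 | 1.24 | 4, 30 | 90% |
| Own level for no previous treatment | six | 0 | 4.5 | 1.07 | 7, 24 | 22% |
| Own level for no previous treatment | three | 0 | 4.5 | 1.07 | 1, 30 | 54% |
| Sum-to-zero | six | 0 | 18 | 1.25 | 8, 24 | 74% |
| Sum-to-zero | three | 0 | 18 | 1.25 | 2, 30 | 96% |
| Period 1 merged with after-placebo | six | −7.1 | 11.25 | 1.16 | 8, 24 | 50% |
| Period 1 merged with after-placebo | three | −22.8 | 7.2 | 1.11 | 2, 30 | 62% |

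Bias is proportional to drift: −0.375d with six orders and −1.2d with this cyclic set. Adding period makes it zero in every row. Uneven orders can also bias the model without period and carryover: at most 2.7 units at d = 20 with 22 patients on six orders.

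**Step 4: what period 1 alone can do.** 18/3 = 6 and 22/3 ≈ 7 patients per arm. A two-sample t test with SD 38, difference 57 and alpha 1.67% has power 0.44 and 0.53, against the planned 90%. Treating the rule and the period-1 test as roughly independent, overall power at d = 19 is about 0.67 × 0.44 + 0.33 × 1.00 = 0.62 (n = 18) or 0.82 × 0.53 + 0.18 × 1.00 = 0.61 (n = 22).

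**Step 5: ketamine-magnesium periods.** If they were pooled with ketamine and magnesium lowered the AUC by a further 20 (assumed), the ketamine effect would read (57 + 77)/2 = 67. If they are a third level, or left out, this does not happen.

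**The case against.** The drift is an assumption. Entry requires chronic pain for more than three months but sets no minimum pain score, so no entry threshold forces regression to the mean. The Sample size section also reports stable pain from 28 to 60 days in the centre's data. This stands as a limit on the size: at 5 units per period the harm is slight. It does not exclude a trend over 15 weeks, and the period term is there because such a trend cannot be ruled out beforehand.

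A reader might infer that the omission biases the ketamine effect outright. The documents do not support that. With balanced orders the estimate is unbiased unless the carryover term takes one particular coding, which the article does not state. Without a carryover term the test is conservative, and before the fallback rule power for 57 stays at about 0.98 or more even at a drift of 35.

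A reader might also infer that treatment is coded with two levels, so that ketamine-magnesium periods are pooled or thrown away. The parenthesis may only name the contrast of the primary objective. The following paragraph uses an omnibus test with Tukey-Kramer comparisons, which presupposes three levels. What remains is that the primary model does not say. This gap does not itself cause time-trend bias.

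Finally, the fallback rule offers some protection, since period 1 is free of time-trend bias. That is true, but the price is the power loss in Step 4.

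**Conclusion.** The point holds. The listed effects omit period, and the omission extends to the secondary outcomes. At an assumed drift of 19 AUC units per period, with six balanced orders and no carryover term, the standard error is about 24% too large, and the period-1 rule fires in about 67 to 82% of trials with no real interaction, leaving 6 to 7 patients per arm. The rule is the most damaging consequence; across the carryover codings and order sets examined at n = 18 it fires in 22 to 96%. Bias of about 7 units (12% of the target 57) or about 23 units (40%) is conditional on the merged carryover coding, with a smaller amount possible from uneven orders. All sizes rest on the assumed drift and order sets; the missing term does not. The paired Wilcoxon fallback also ignores period, but replacing it is a matter of preference.

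**What to change.** In the Statistical analysis section:

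1. Add period (1, 2, 3) as a fixed effect in the primary and secondary crossover models.
2. State treatment as three levels (placebo-placebo, ketamine-placebo, ketamine-magnesium), with ketamine-placebo minus placebo-placebo as the primary contrast.
3. Run any sequence-by-treatment or carryover check only with period in the model, report it as a check, and delete the rule that moves the primary analysis to period 1.

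Replacing the paired Wilcoxon fallback is optional.

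The cost is a few lines of text and 2 degrees of freedom (34 to 32 for error at n = 18 without a carryover term). If a carryover term stays, the order set and coding should be stated with it. At n = 18 with three cyclic orders, period and carryover together raise the SE of the contrast from about 9 to about 20 and leave no degrees of freedom for a sequence-by-treatment test. With six orders the SE rises only to about 10.

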**Methods/design:**

A randomized, double-blind, crossover, placebo-controlled study will be performed in Clermont-Ferrand University Hospital, Clermont-Ferrand, France. The aim is to evaluate the effect of ketamine with or without magnesium in 22 patients with neuropathic pain. Intravenous ketamine/placebo, ketamine/magnesium sulfate, or placebo/placebo will be administered consecutively to each patient, in random order, once at 5-week intervals. The primary endpoint is the AUC of pain intensity assessed on a 0–10 Numeric Pain Rating Scale for a 5-week period. Data analysis will be performed on an intention-to-treat basis, and all statistical tests (except primary analysis) will be performed with an α risk of 5% (two-sided).

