### Sample size calculation

To highlight the analgesic efficacy of intravenous ketamine in patients with intractable NP, sample size estimation was based on a pilot study done at the pain clinic of the University Hospital of Clermont-Ferrand (administration of intravenous ketamine in a similar open-label population), showing an AUC (28 days) of the intensity of pain of 164 ± 38 (unpublished data). Furthermore, in a study comparing similar treatments (ketamine and placebo) in a different chronic pain setting (CRPS), the AUC graph estimate suggested a 35% reduction in AUC (at 28 days), that 18 patients are needed to detect a minimum difference of 57 in the primary outcome, with a two-sided type I error of 1.67% (to take account of multiple comparisons), statistical power of 90%, and an intraindividual correlation coefficient of 0.5 (owing to the crossover design and no carryover effect assumed) [46]. Considering data from our center, a recent study [46] (NCT01602185) currently submitted to a peer-reviewed journal but not yet published clearly shows that pain evaluation remains the same from 28 days to 60 days. Ultimately, allowing for patient dropout for adverse events or premature withdrawal, we plan to recruit 22 subjects.

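### A sequence × treatment pre-test can reduce the primary analysis to an unsized first-period comparison of 7 to 8 patients per arm, and a plain time trend can trigger it

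*Protocol article*

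**What the plan says.** The Statistical analysis section compares the AUC of pain intensity by a crossover repeated-measures ANOVA. The listed effects are treatment, sequence, subject (random) and carryover; period is not among them. A sequence × treatment interaction is tested next, and "if it is significant, statistical analysis will cover only the first period of the crossover study". Secondary scores are to be handled in the same way as the primary endpoint.

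The Sample size calculation section plans only for the full within-patient comparison. It takes a pilot result of "an AUC (28 days) of the intensity of pain of 164 ± 38", a "minimum difference of 57 in the primary outcome", "statistical power of 90" per cent, and an intraindividual correlation of 0.5, "owing to the crossover design and no carryover effect assumed". It gives no power for a first-period analysis.

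The significance level is worded in three places. The sample size is calculated "with a two-sided type I error of 1.67% (to take account of multiple comparisons"). The Abstract says that "all statistical tests (except primary analysis) will be performed with an α risk of 5% (two-sided"). The Statistical analysis section sets the analysis "for a two-sided type I error at α = 5" per cent, with no exception for the primary endpoint.

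**The concern.** In period 1 each patient has received one of three treatments. A first-period analysis is therefore a three-arm parallel comparison on a third of the data, without the within-patient pairing that the sample size relies on. Which of the two analyses answers the primary question is left to a preliminary test.

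That test is a poor guide. With three treatments in three periods, knowing a patient's order and treatment tells you the period. Any change in pain over calendar time therefore falls into the sequence × treatment interaction unless period is modelled separately. A trend common to all patients is harmless to an all-period model that includes period, yet here it could cause two thirds of the data to be thrown away.

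**Working it through.** **Inputs.** From Sample size calculation: difference 57 (35% of 164 = 57.4), SD 38, correlation 0.5, two-sided alpha 1.67%, power 90%, 18 patients needed, 22 recruited. Assumed: equal allocation of first-period treatments, so 22/3 = 7.3, that is 7 or 8 per arm. The pre-test is taken at 5%.

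**The plan's own figure.** SD of the within-patient difference = 38 × √(2 × (1 − 0.5)) = 38. Then n = ((2.393 + 1.282) × 38/57)² = 2.45² = 6.0, or 10 with the t distribution. The stated 18 is not reproduced. With 18 patients these inputs give 99.97% power, so the full crossover has ample power on the article's assumptions.

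**First-period power.** Two-sample t-test, non-central t, non-centrality = 57 / (38 × √(1/n₁ + 1/n₂)):
- 7 v 7: 57/20.31 = 2.81. Power is 53.1% at 1.67% and 73.1% at 5%.
- 8 v 7: 57/19.67 = 2.90. Power is 57.3% at 1.67% and 76.4% at 5%.
- 6 v 6 (18 patients): 57/21.94 = 2.60. Power is 43.5% at 1.67%.

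Other methods for 7 v 7 at 1.67% give 58.0% (error pooled over three arms) and 66.0% (normal approximation). The normal approximation at 5% gives 80.1%. All are below 90%. Scaling both the difference and the SD from 28 to 35 days leaves 53%.

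**How often the rule fires.** Simulation of 22 patients over six orders. At correlation 0.5 the patient and residual variances are each 38²/2 = 722. The drift sizes are assumptions. Over a 35-day AUC, 9.5 units is 9.5/35 = 0.27 NPRS points and 19 units is 0.54 points.

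| Drift per period | Fires, carryover term kept | Fires, carryover term left out | Overall power at 1.67% |
|---|---|---|---|
| 0 | about 5% | about 5% | about 98% |
| 9.5 | about 9–17% | about 23% | about 90–96% |
| 19 | about 28–64% | about 81–82% | about 65–89% |

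The range with the term kept reflects different codings of carryover. As a check, overall power ≈ 1 − (trigger rate) × (1 − 0.573), because the all-period analysis has nearly 100% power:
- 9% gives 96%, and 23% gives 90%.
- 28% gives 88%, and 82% gives 65%.

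**Response to carryover.** With the listed carryover term kept, true first-order carryover of 25 or 51 units leaves the trigger rate at about 5% and overall power at about 98%. The interaction then tests what is left after carryover has been adjusted for.

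**Type I error.** Under no treatment effect the two-step rule gave 1.5 to 1.8% against a nominal 1.67%.

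**The case against.** The strongest defence is that the rule rarely does harm. With no drift it fires about 5% of the time and overall power is about 98%, above the planned 90%. At 9.5 units of drift overall power is still at least about 90%. A serious loss needs a drift near 19 units per period, which is 2 × 19 = 38 units from the first period to the third, a full SD. The article gives no drift size. This stands, and it means that 53 to 57% must not be read as the power of the trial.

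A reader might also infer that real carryover would nearly always trigger the fallback. That follows only if the carryover term is left out before the interaction is tested: a carryover of 51 units then fires it 99.7% of the time, with 57% overall power. The article lists carryover in the model and tests the interaction afterwards, so the text does not support this.

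Nor does it follow that carryover must be in the primary model. With all six orders it costs little (power stays about 100%). With a three-sequence Latin square the same model has only about 74% power for 57 units at 1.67%. The article does not state the number of sequences.

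Finally, the 5% wording in the Statistical analysis section would raise first-period power to 73–76%. The Abstract and the Sample size calculation support 1.67% for the primary comparison, and either level misses 90%.

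**Conclusion.** The concern holds in this form: the article fixes a data-dependent rule that can replace the sized within-patient analysis with an unsized between-patient one. Conditional on the rule firing, power is about 53% (7 v 7) to 57% (8 v 7) at 1.67%, or 73–76% at 5%. Unconditionally, power runs from about 98% with no trend to about 65–89% at the larger assumed drift.

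The rule has no compensating benefit. With the carryover term kept, it fires by chance or on a time trend, and a period effect would absorb the trend. With the term left out, it discards data that the listed term could adjust. A reader who knows the criticism of pre-testing in the two-period crossover might expect false positives to be inflated; the simulations do not show that here. The harm is lost power and lost data.

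The conditional figures rest on SD 38 and equal first-period allocation. If 18 patients were right because variability is larger, an SD of about 60 to 66 would be needed, and 7 v 7 power would be about 17–21%, so 53–57% is not pessimistic. The trigger rates also rest on six orders and the assumed drifts.

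**What to change.** Delete the interaction pre-test and the first-period-only rule. State one primary analysis: a mixed model on all periods with three-level treatment, period, sequence and random patient. The ketamine minus placebo contrast is the result whatever any carryover or interaction p-value shows.

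Decide before unblinding, from the sequences actually used, whether first-order carryover belongs in that model. With all six orders it can be included at little cost. With a three-sequence Latin square, leave it out of the primary model and report the carryover-adjusted fit as a sensitivity analysis. Report the first-period estimate as a sensitivity analysis only. Apply the same wording to the secondary scores.

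The cost is a change of wording in the Statistical analysis section, or in the analysis plan, before unblinding. It needs no further patients or data.

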#### Secondary outcome measure

Secondary endpoints are the evaluation of pain (NPRS, NPSI, BPI, McGill Pain Questionnaire, PGIC), anxiety and depression (HADS), quality of life (SF-36), and quality of sleep (PSQI) using a variety of scales and questionnaires. Furthermore, the intensity of the average and maximum pain scores as well as concomitant analgesic treatments will be reported in a daily pain diary. The various assessments and questionnaires are summarized in Fig. 2.

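### PGIC, an ordered secondary outcome, may be tested with Stuart-Maxwell, which ignores category order and cannot carry the crossover effects; with five or more categories and a moderate shift much power is lost

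*Protocol article*

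**What the plan says.** PGIC is one of the secondary pain measures. The Secondary outcome measure section reads: "Secondary endpoints are the evaluation of pain (NPRS, NPSI, BPI, McGill Pain Questionnaire, PGIC". The Statistical analysis section groups it with analgesic response as a categorical parameter and offers two methods: "the Stuart-Maxwell test for proportion paired data or a generalized linear mixed model will be used, taking the above effects into account". The effects meant in that closing condition are those listed for the primary crossover ANOVA: "treatment group (ketamine versus placebo), sequence, subject (as random effect), and carryover".

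The design has three treatments per patient. Under Regimen: "Each patient will receive successively in random order each of the three products". The section opens with a general two-sided 5% level. The 1.67% level appears in the Sample size calculation, which concerns the AUC. No rule is given for choosing between the two methods, the mixed model is not described as ordinal, and neither the number of PGIC categories nor a PGIC effect is stated.

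**The concern.** A global impression of change runs from worse to better. The question is whether patients improve more under one treatment than another, which is a shift along an ordered scale. Stuart-Maxwell asks something else: whether each category has the same marginal proportion under two treatments. It spends up to K − 1 degrees of freedom on any marginal difference, including one with no net improvement. With about 20 pairs spread over several categories, its chi-square reference is also conservative.

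The test is computed from a single square table of paired responses. It takes two of the three treatments and has no place for sequence or carryover. An analyst could choose it, comply with the protocol, and report a moderate PGIC benefit as non-significant beside a positive AUC result, purely because of the test.

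**Working it through.** **Can the test meet the sentence's own condition?** The effects listed are treatment, sequence, random subject and carryover. For a K × K table of paired responses with counts n_ij, Stuart-Maxwell uses d_i = n_i. − n_.i, V_ii = n_i. + n_.i − 2n_ii, V_ij = −(n_ij + n_ji), and X² = d′V⁻d on rank(V) ≤ K − 1 degrees of freedom. Pairing handles the subject. Sequence and carryover appear nowhere, and a third treatment cannot enter. Relabelling the categories leaves X² unchanged, so order is not used. This step needs no assumption about PGIC.

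**What does it cost?** The article states no PGIC power, so there is no figure to reproduce.

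Inputs from the article: 18 patients needed, 22 recruited and correlation 0.5 (Sample size calculation); two-sided 5% (Statistical analysis). Assumed: a latent normal scale cut into K equally likely categories, K = 2, 3, 5 or 7, and a true shift in latent SD units. The comparator is a tie-corrected signed-rank test on the within-patient score differences, Z = Σ sign(D)R / √ΣR². There were 4,000 simulated trials per setting, so the simulation standard error is at most √(0.25/4000) = 0.8 points.

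Power at a 0.75 SD shift:

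| Categories | n | Stuart-Maxwell | Ordered paired test | Loss (points) |
|---|---|---|---|---|
| 7 | 18 | 10% | 77% | 67 |
| 7 | 22 | 28% | 85% | 57 |
| 5 | 18 | 27% | 74% | 47 |
| 5 | 22 | 44% | 83% | 39 |
| 3 | 18 | 48% | 66% | 18 |
| 3 | 22 | 59% | 75% | 16 |

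(The row for 3 categories at n = 18 comes from a run of 3,000 trials with a one-degree-of-freedom paired score test, ΣD/√ΣD², as comparator. It behaves almost identically to the signed-rank test.) With two categories the tests coincide, because both reduce to McNemar.

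**Where the loss comes from.** Degrees of freedom explain part of it. A one-degree-of-freedom power of 80% falls to 71% at 2 df, 60% at 4 df and 52% at 6 df. The rest is small-sample conservatism: with 7 categories the actual type I error of Stuart-Maxwell is about 0.4% at n = 18 and 1.2% at n = 22, against 4 to 5% for the ordered test.

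**Sensitivity.**
- Peaked 7-category distribution with 45% in the middle category (n = 22, 0.75 SD): 33% v 86%.
- Correlation 0.2, a differently peaked 7-category distribution, 0.8 SD: 10% v 67% at n = 18 and 20% v 76% at n = 22.
- Shift 1.0 SD, n = 22: 54% v 98% (7 categories), 75% v 97% (5), 85% v 93% (3).
- Shift 1.5 SD, the size of the planned AUC effect (57/38 = 1.5): Stuart-Maxwell reaches about 93%, 98% and 98% at n = 22 for 7, 5 and 3 categories, and about 67%, 89% and 96% at n = 18. The ordered test is already at 97 to 100% by 1.3 SD. The loss is therefore about 33 points with 7 categories at n = 18, and at most about 11 points (5 categories, n = 18) elsewhere.

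**The case against.** The strongest reply is that the same sentence permits a generalized linear mixed model. Such a model can carry all three treatments and the crossover effects and, with a cumulative link, the category order. The closing condition could also be read as attaching only to the model, which would remove the contradiction. The loss then arises only if Stuart-Maxwell is chosen, or if the model is fitted as nominal. That limits the point but does not answer it: Stuart-Maxwell remains an authorised analysis under either reading, and nothing in the text calls the model ordinal. Link function and coding may be left to a statistical analysis plan; the objection here is to a method the article names.

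A reader might infer that most of the power for PGIC is lost at this sample size. The documents do not support that in general. It holds for about 7 categories, or 5 at n = 18, with shifts of about 0.75 SD or less. It fails for 3 categories, and at n = 22 a 1.0 SD shift is detected more often than not at every category count examined. The 0.75 SD is an assumption, whereas the only planning effect in the article is 1.5 SD, for AUC. That effect need not carry over to PGIC, and magnesium's increment over ketamine, a secondary objective, may well be smaller than the whole ketamine effect. If PGIC is collapsed to responder status, the loss vanishes.

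It is also true that PGIC is unpowered and secondary, and that the error is in the conservative direction, so no false claim of benefit follows from it.

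**Conclusion.** The point holds in a limited form. As one of two permitted analyses of an ordered outcome, the protocol names a test that ignores the order, handles only two of three treatments and cannot take sequence or carryover into account. That part rests on the text alone.

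The size of the loss is conditional on a latent-normal model with correlation 0.5, 18 to 22 complete pairs, 5 to 7 categories and a 0.75 SD shift. There it is about 40 to 65 points; with 3 categories it is about 15 to 18. The text does not commit the trial to Stuart-Maxwell, so this is a risk under one permitted choice and not a certain result. The AUC analysis, the sample size and the primary conclusion are untouched. It is a worthwhile, inexpensive improvement to a secondary analysis.

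**What to change.** In the Statistical analysis section, remove Stuart-Maxwell for PGIC. State that PGIC is analysed as an ordered outcome with a cumulative-logit mixed model containing three-level treatment, the crossover effects and a random subject effect, and that odds ratios with confidence intervals are reported for ketamine v placebo and for ketamine-magnesium v ketamine. This specifies the mixed model that the sentence already allows.

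Take the p-value from a within-patient permutation of the model statistic, or support the model with a paired signed-rank test on PGIC scores, because the asymptotic likelihood-ratio test is somewhat liberal at this size (6 to 9.5% in 200 simulated trials at a nominal 5%). Keep McNemar or a logistic mixed model for the binary analgesic response.

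The cost is one sentence, a proportional-odds assumption and slightly more analysis work. No new data are needed. Recruitment was ongoing when the article appeared, so the choice could be fixed before unblinding.
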